### Measurements

Table 1 provides an overview of interviews and self-report assessments at the different time points. Within 14 days before the start of a TBT-S-week, clinician-administered interviews will be conducted, and pre-assessment forms will be completed in both treatment arms. Post-assessments will be completed within 12 days after the last day of the TBT-S week and follow-up assessments within a 20 day period centered at 3-, and 12 month follow-ups. Use of health care services will be assessed at pre-assessment and at 3-, 6-, 9-, and 12-months follow-ups. The primary endpoint will be the group difference in change in eating disorder psychopathology (Eating Disorder Examination Questionnaire [EDE-Q (Fairburn and Beglin, 1994)] Global score) from pre-assessment to 3- month follow-up. The Norwegian version of EDE-Q has shown satisfactory psychometric properties (Rø et al., 2015; Reas et al., 2011). Interviews performed at pre-assessment are the Mini International Neuropsychiatric Interview [M.I.N.I. 7.0.2 (Sheehan et al., 1998)] and the Eating Disorder Assessment for DSM-5 [EDA-5 (Sysko et al., 2015; Dahlgren et al., 2020)] which are administered to assess comorbidities and confirm the AN/AAN diagnosis self-reported by the patient. When travel time to the main recruitment site (Oslo university hospital) allows for in-person assessments, participants are invited to fill out the forms on site, where weight and height will also be measured and registered. All other participants will complete the self-report assessments remotely and self-report weight and height. The M.I.N.I. and EDA-5 interviews of these patients will be conducted via a secure digital video platform. The main tools used for assessment are all previously validated and well-established measures (Akoury et al., 2018; Bouwmans et al., 2013; Cejalvo et al., 2025; Dambi et al., 2018; Feng et al., 2021; Fowler et al., 2014; Gratz and Roemer, 2004; EuroQol Group, 1990; Hibbs et al., 2014; Hoefman et al., 2013; Håseth et al., 1990; Osman et al., 2012; Pedersen et al., 2022; Sepulveda et al., 2009; Spielberger, 1970; Timman et al., 2015; Wiedemann et al., 2002; Winkler et al., 2019). Utilization of health care services and data on resource use will be collected using the self-reported Treatment Inventory of Costs in Patients with psychiatric disorders (TIC-P) questionnaire (Bouwmans et al., 2013; Timman et al., 2015). To ensure a detailed characterization of TAU, additional items on eating disorder service utilization have been added. These include whether the participant is currently receiving ED treatment, level of care and treatment intensity, as well as type of therapy and treatment modality. This information on service utilization together with the EuroQoL 5D [EQ-5D (Feng et al., 2021; Group, 1990)] and the Care-related Quality of Life instrument [CarerQol-VAS (Cejalvo et al., 2025)] will be used to assess the potential cost-effectiveness of TBT-S. Cost will be examined from both the healthcare provider as well as the societal perspective. Norwegian translations of all measures will be used. Two of the measures (Accommodation and Enabling Scale for Eating Disorders and Eating Disorder Quality of Life Scale) have not been validated in Norwegian. TBT-S attendance will be assessed at post-assessment (TBT-S plus TAU group only) using a study specific question added to the Client Satisfaction Questionnaire, asking participants to report how many of the five TBT-S treatment days they attended. At the 3- and 12- month follow-ups, adherence to TBT-S treatment recommendations will also be assessed using self-report measures, including the extent to which participants who received TBT-S have utilized the treatment tools provided during the treatment week.

**Table 1 tab1:** Overview of study timeline and measures.

		Timeline						
Assessments		Pre-assessment	TBT-S week*	Post-assessment	3 months	6 months	9 months	12 months
BMI^†^		x			x			x
Clinical interviews								
MINI		x						
EDA-5		x						
Questionnaires (pt)								
EDE-Q		x		x	x			x
CIA		x		x	x			x
EQ-5D		x			x			x
Carer QoL-VAS		x		x	x			x
Motivation VAS		x		x	x			x
EDQLS		x			x			x
MSPSS		x			x			x
DASS		x			x			x
STAI		x		x	x			x
CSQ-8				x				
DERS-SF		x		x	x			x
TIC-P		x			x			x
Health Services for ED		x			x	x	x	x
Treatment Adherence					x			x
Questionnaires (su)								
DASS		x			x			x
AESED		x			x			x
FQ		x			x			x
EQ-5D		x			x			x
Carer QoL-VAS		x			x			x

Note: TAU, Treatment as usual; TBT-S, Temperament based therapy with support; BMI, Body Mass Index; MINI, Mini International Neuropsychiatric Interview; pt, patients; su, supports; EDA-5, Eating Disorder Assessment for DSM-5; EDE-Q, Eating Disorder Examination Questionnaire; CIA, Clinical Impairment Assessment; EQ-5D, EQ-5D health-related quality of life questionnaire; QoL, Quality of life; VAS, Visual analogue scale; EDQLS, Eating Disorder Quality of Life Scale; MSPSS, Multidimensional Scale of Perceived Social Support; DASS, Depression Anxiety Stress Scale; STAI, State–Trait Anxiety Inventory; CSQ-8, Client Satisfaction Questionnaire; DERS-SF, Difficulties in Emotion Regulation Scale Short Form; TIC-P, Treatment Inventory of Costs in Patients with psychiatric disorders; ED, eating disorders; AESED, Accommodation and Enabling Scale for Eating Disorders; FQ, Family questionnaire. *Only participants in intervention group. †Height and weight of participants at the main recruitment site will be measured when travel time allows for in person assessments.

#### Implementation fidelity and therapists’ competence

The five key treatment components of TBT-S will be rated for degree of fidelity (10-point scale from 0 = No adherence; the section was skipped to 10 = Perfect; the treatment component was presented as advised in the manual). Therapist competence will be rated with 12 items (e.g., therapist delivering neurobiological lectures express ideas clearly and at an appropriate pace) using a 100-point scale with anchors for each item (e.g., 20 = Poor; therapists are difficult to follow and lecture proceeds at an uncomfortable pace, 100 = Superior; therapists are unusually articulate and express ideas in ways that all group members understand; perfect pace).

### Sample size calculation

The sample size calculation is conducted based on the primary outcome, global EDE-Q score at 3-month follow-up. It is informed by data from a feasibility study conducted by the authors (Stedal et al., 2023), in which the *SD* of the change in global EDE-Q from baseline to post-treatment was 0.87. A between-group difference in global EDE-Q change of 0.44 was assumed, based on the study by Tregarthen et al. (2019), who defines 0.5*SD as a clinically relevant difference in change from baseline, corresponding to a medium effect size (Cohen’s *d* = 0.5). In a two-sided test of superiority with *α*-level = 0.05 and 80% power, a total sample size of 126 is required. Participants are allocated to study arms in a 1:1 ratio. To account for the observed correlation (*p* = 0.732) between baseline and 3-month follow-up as reported in our previous feasibility study (Skoog et al., 2025), an ANCOVA framework is employed in the sample size calculations using raw EDE-Q global score at 3-month follow-up while adjusting for baseline. Thus, the number of participants is multiplied by the factor (1 + *p*)/2. Applying the correlation *p* = 0.732, the multiplicative factor is (1 + 0.732)/2 = 0.866. This results in an estimated required sample size of 110 participants. Assuming 10% attrition rate, we will include a total of 120 participants.

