**Methods:**

In this multicenter randomized controlled trial (RCT), 120 adults with a diagnosis of AN or atypical AN (AAN) will be randomized to receive either TBT-S in addition to TAU or TAU alone. Individuals with AN/AAN and their supports will complete assessments before and after the TBT-S treatment week, and at 3- and 12-month follow-ups. The primary outcome is change in eating disorder symptomatology from baseline to the 3-month follow-up. Secondary outcomes include changes in quality of life, psychological health, body mass index (BMI), and health care utilization, as well as changes in quality of life and caregiving experience among supports.

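### Minor: the printed requirement of 110, the 10% attrition and the total of 120 do not agree, because 10% lost from 120 leaves 108

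*Protocol article*

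**What the plan says.** All the figures are in the Protocol article, section Sample size calculation.

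- **Effect and spread.** "A between-group difference in global EDE-Q change of 0.44 was assumed". The SD comes from the feasibility study, where that of the "change in global EDE-Q from baseline to post-treatment was 0.87". The section also describes the effect as half an SD, Cohen's d = 0.5.
- **Test.** "In a two-sided test of superiority with" alpha "level = 0.05 and 80% power, a total sample size of 126 is required". "Participants are allocated to study arms in a 1:1 ratio".
- **Baseline adjustment.** The 126 is multiplied by (1 + 0.732)/2 = 0.866. "This results in an estimated required sample size of 110 participants".
- **Attrition.** "Assuming 10% attrition rate, we will include a total of 120 participants".

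The abstract repeats the total: "120 adults with a diagnosis of AN or atypical AN (AAN) will be randomized". The section names neither the formula behind 126 nor the one used for attrition, and it does not say whether rounded or unrounded values were carried from step to step.

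**The concern.** A reader who follows the printed steps takes 110 as the number that must contribute the 3-month outcome, applies the 10% loss, and expects a total of at least 122. The article gives 120. Read the other way, 120 with 10% loss supplies fewer participants than the section says are required.

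What is at stake is the justification of the trial's headline number, which should be reproducible from the figures printed beside it. If the step were badly wrong, the trial could also fall short of its stated 80% power, so the size of the gap has to be checked.

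**Working it through.** **Inputs** (Protocol article, Sample size calculation): difference 0.44; SD of change 0.87; two-sided alpha 0.05; power 80%; 1:1 allocation; factor 0.866; attrition 10%.

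**1. Reproducing 126.** For two means, the normal approximation is n per arm = 2 × [SD × (1.960 + 0.842) / difference]².

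| Effect | Formula | n per arm | Total |
|---|---|---|---|
| 0.44/0.87 = 0.506 | normal | 61.37, so 62 | 124 |
| 0.44/0.87 = 0.506 | t-test | 62.35, so 63 | 126 |
| d = 0.5 exactly | normal | 62.79, so 63 | 126 |
| d = 0.5 exactly | t-test | 63.77, so 64 | 128 |

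The stated 126 reproduces in two ways.

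**2. Reproducing 110.** 126 × 0.866 = 109.1, rounded up to 110. This reproduces.

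**3. The attrition step from the printed 110.**

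- Completers from 120: 120 × 0.90 = 108, two below 110.
- Inflation by division: 110 / 0.90 = 122.2, so 123, or 124 for equal arms.
- Cruder inflation by multiplication: 110 × 1.10 = 121.
- Attrition that 120 can absorb: 1 − 110/120 = 8.3%.

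Neither way of inflating 110 by 10% gives 120.

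**4. The same step without intermediate rounding.** The t-test total at 0.44/0.87 is 2 × 62.347 = 124.69. Then 124.69 × 0.866 = 107.98 completers, and 107.98 / 0.90 = 119.98, which is 120. Another route, 109.116 × 1.10 = 120.03, also lands on 120 to the nearest whole number.

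**5. What two completers are worth.** The SD after baseline adjustment is 0.87 × √0.866 = 0.81. By the normal approximation, power = Φ[difference / (0.81 × √(4/N)) − 1.96]. For N = 108 and 0.44 the standard error is 0.156, so power = Φ(2.824 − 1.960) = Φ(0.864) = 80.6%. The full set is:

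| Completers | Difference | Normal | t-test |
|---|---|---|---|
| 108 | 0.44 | 80.6% | 79.9% |
| 110 | 0.44 | 81.3% | 80.6% |
| 108 | 0.435 (d = 0.5) | 79.7% | 79.0% |
| 110 | 0.435 (d = 0.5) | 80.4% | 79.7% |

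Going from 110 to 108 costs about 0.7 percentage points in every column.

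**The case against.** The strongest defence is step 4 of the working: the stated difference and SD, carried through unrounded with a t-test, need 107.98 completers and 119.98 randomised. A reader might infer that 120 cannot be obtained from the plan's inputs. That reading fails, since 120 does follow from 0.44 and 0.87 on this route. What the defence does not rescue is the printed text. The article does not report this route, and it calls 110 the required size. If about 108 was the real requirement, the 110 is the figure to correct.

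The second defence is that the linear mixed model (Statistical analysis) keeps participants with incomplete follow-up. This stands in part. Someone with a post-assessment EDE-Q but no 3-month value adds some information, while someone with a baseline only adds no outcome. It softens a shortfall of two, but the article does not use it to justify 120.

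Two stronger readings are tempting, and the document does not support them.

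- **That 126 should have been 128.** The larger figure arises only from the t-test at exactly d = 0.5. The normal approximation at the same effect gives 126, and the article names no formula. This is a choice of method, and 0.44 is ordinary rounding of 0.5 × 0.87 = 0.435.
- **That the 10% leaves out participants lost before the pre-assessment.** The full analysis set does require a pre-assessment EDE-Q, but the article does not define what its 10% covers. Nothing shows that such losses fall outside it.

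**Conclusion.** The point holds as a minor correction to a stated figure. The printed 110, 10% and 120 are mutually inconsistent by two completers, or by three to four randomised participants (123 or 124 against 120).

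Power at 108 completers is 79.0% to 80.6%, against a target of 80%. A reader might infer that the trial is underpowered because of this step. It is not: the loss is about 0.7 percentage points. These figures take the plan's own SD, correlation and difference as given, and count only participants with the 3-month outcome.

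**What to change.** Rewrite the last sentence of the Sample size calculation section in one of two ways:

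- state that 120 randomised allows for about 8% attrition from a required 110; or
- state that 10% attrition from 120 leaves 108 analysed, giving about 80% power for a difference of 0.44.

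If about 108 was the requirement actually computed, also replace the printed 110 and say that unrounded values were carried forward. Naming the formula would make the chain reproducible.

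The cost is one corrected sentence. The total of 120 in the abstract can stay, and no extra recruitment is needed. The only price is that the stated margin becomes slightly less favourable.

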### Statistical analysis

Primary analyses will be conducted on the *Full Analysis Set* (FAS), defined as all participants who were randomly assigned to a treatment arm and who provided, at minimum, the following pre-assessment data; for individuals with AN/AAN, the EDE-Q; and for supports, at least one completed questionnaire, irrespective of the measure. As a sensitivity analysis for the primary outcome, the primary endpoint analysis will also be conducted on the *Per-protocol* (PP) population. In the TBT-S + TAU arm, the PP population will comprise those in the FAS who attended at least four of the five TBT-S days. In the TAU arm, the PP population will be identical to the FAS, as no additional intervention is delivered. Per protocol analyses will be adjusted for the time interval between randomization and pre-assessment.

The superiority of TBT-S plus TAU over TAU alone for the primary outcome will be analyzed using a linear mixed model with the 3-month EDE-Q global score as a continuous outcome, with baseline EDE-Q, treatment arm and study site, Time (factor) and Time (factor)*treatment arm interaction as fixed effects and subject ID as random effect. Secondary outcomes will be analyzed using linear mixed models in which baseline value, treatment arm, study site, time and time*treatment arm-interaction are included as fixed effects, and subject ID is included as random effect. The use of mixed linear models will allow for including in the analyses also participants that do not complete all assessments. As participants in the TAU alone condition may opt to receive the intervention after their 3‑month assessment, a proportion of TAU alone participants will undergo post‑3‑month treatment crossover. Analyses that include 6‑, 9‑, or 12‑month follow‑up will therefore incorporate analytic strategies appropriate for partial crossover. Further details of the statistical analyses will be specified in a statistical analysis plan, which will be completed before the database is locked and analyses commence.

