The study has some potential limitations which are worth noting, some of which could impact the ability to interpret potential improvements. For example, the participants in the TBT-S arm will receive 35–40 h of additional treatment which is not controlled for in the control group. Thus, it will be uncertain if any improvements in the TBT-S group could be attributable to the increased dose of treatment, and/or non-specific elements in the TBT-S group (e.g., placebo, peer-support, behavioral activation). Nevertheless, this RCT marks an important first step in deciphering whether TBT-S in addition to TAU could improve treatment outcomes, and future studies might wish to include a comparison group program of similar intensity, with as little overlap as possible with TBT-S, thereby increasing the chances of better attributing any changes to TBT-S. Further, being allocated to TAU could be discouraging for some participants, increasing the risk of drop-out for this group. In addition, currently there are no other clinics in Norway offering adult TBT-S for AN/AAN. However, this could change over time and there is a risk that the TAU group gets tainted by TBT-S from a treatment provider not included in the study. Travel costs are covered through, a public service that reimburses travel expenses for healthcare treatments and clinical trials, and most employers will provide either paid or unpaid leave to receive healthcare. However, some eligible participants may still be prevented to participate in the study because they are not able to take time off work to attend TBT-S. Furthermore, the power analysis were based on our feasibility study with a comparable population. Even so, since both groups in this RCT will be receiving active treatments, there is a risk that potential differences between groups could be obscured by varying treatment settings and intensities, which would be expected to achieve reasonable effect sizes on their own. In addition, the timing of TBT-S within participants’ ongoing treatment is not standardized. As TBT-S is designed to be flexibly integrated into routine clinical care, participants may receive the intervention at different points in their treatment trajectory, which could contribute to heterogeneity in treatment response and introduce potential floor or ceiling effects. Finally, the lack of baseline assessment before randomization could result in the study’s pre-assessment being biased by the randomization. We will perform analyses of pre-assessments to check that the randomization produced equivalent groups. Any differences will be controlled for.

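### The per-protocol sensitivity analysis selects attenders in the TBT-S arm only, so it is not protected by randomisation and gives little reassurance about the primary result

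*Protocol article*

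**What the plan says.** All references are to the Protocol article. Under Statistical analysis, the primary analysis is on the FAS: everyone randomised who gave a pre-assessment EDE-Q. One sensitivity analysis is named for the primary outcome, a PP analysis. Its TBT-S arm is restricted to FAS members who attended four or five of the five days. Its control arm is unrestricted: "In the TAU arm, the PP population will be identical to the FAS, as no additional intervention is delivered". The only adjustment specific to the PP analysis is for the interval between randomisation and pre-assessment.

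Under Measurements, one attendance measure is described. It is a question added to the satisfaction questionnaire at post-assessment, given in the TBT-S arm only, "asking participants to report how many of the five TBT-S treatment days they attended". Table 1 shows that questionnaire at post-assessment and at no other visit.

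The Discussion also accepts that "there is a risk that the TAU group gets tainted by TBT-S from a treatment provider not included in the study". The PP definition does not mention such participants, so they stay in the TAU set.

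**The concern.** TAU participants who would not have managed four days of TBT-S stay in the PP analysis, while their counterparts in the TBT-S arm are taken out. The reason given, that TAU delivers nothing extra, explains why attendance cannot be observed there. It does not make the remaining groups comparable. Baseline EDE-Q and study site in the model remove only the part of the difference that they predict, and the waiting-time covariate says nothing about who attends.

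A second filter is possible. If the self-report item defines the PP set, a TBT-S participant who attended all five days and supplies the 3-month EDE-Q, but did not return the post-assessment form, cannot be shown to qualify. A TAU participant who missed the same visit stays in.

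What is at stake is the reading of the result. A sensitivity analysis should show whether the primary conclusion survives a change of assumption. If this one agrees with the FAS, that may be partly selection; if it disagrees, the cause cannot be identified.

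**Working it through.** **1. The plan's own figures.** The Sample size calculation section gives these inputs: "change in global EDE-Q from baseline to post-treatment was 0.87" (the SD); "A between-group difference in global EDE-Q change of 0.44 was assumed"; "Participants are allocated to study arms in a 1:1 ratio"; two-sided alpha 0.05 and 80% power, with "level = 0.05 and 80% power, a total sample size of 126 is required".

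- Normal approximation: n per arm = 2 × (1.960 + 0.842)² × (0.87/0.44)² = 61.4, so 62 per arm and 124 in total. The exact t calculation gives 63 per arm, 126 in total, as stated.
- Baseline adjustment: 126 × (1 + 0.732)/2 = 109.1, rounded up to 110, as stated.
- Attrition: 110/0.90 = 122.2, so 123 against the stated 120, within 3%. Nothing below depends on this.

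**2. Residual SD at 3 months given baseline.** This assumes equal variances at both times and that the SD of change, quoted to post-treatment, also applies at 3 months.

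- SD of EDE-Q = 0.87/√(2 × (1 − 0.732)) = 1.188
- Residual SD = 1.188 × √(1 − 0.732²) = 0.81

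**3. Bias from keeping attenders in one arm when the true effect is zero.** Let p be the share of the TBT-S arm excluded. Let c be the correlation between propensity to attend and a better 3-month residual. The document gives neither, so both are assumptions. For a normal latent propensity:

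bias = c × 0.81 × φ(z_p)/(1 − p), in favour of TBT-S when c is positive.

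| Excluded p | φ(z_p)/(1 − p) | c = 0.2 | c = 0.3 | c = 0.4 |
|---|---|---|---|---|
| 10% | 0.195 | 0.032 | 0.047 | 0.063 |
| 20% | 0.350 | 0.057 | 0.085 | 0.113 |
| 30% | 0.497 | 0.080 | 0.121 | 0.161 |

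At c = 0.3 these are about 11%, 19% and 27% of 0.44. At c = 0 the bias is zero; at negative c it has the same size and the opposite sign.

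**4. Check by simulation.** This used baseline-adjusted regression, 60 per arm, a true effect of zero and 4000 runs per scenario. Mean estimates agree with the formula.

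| Excluded p | Type I error, c = 0 | c = 0.2 | c = 0.4 |
|---|---|---|---|
| 5% | 4.6% | 4.8% | 6.0% |
| 10% | 4.9% | 5.4% | 6.6% |
| 20% | 5.6% | 7.1% | 11.0% |
| 30% | 5.2% | 7.4% | 16.3% |

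**5. Scale.** With 55 per arm (110/2), the standard error is about 0.81 × √(2/55) = 0.15. At 10% excluded, the largest tabulated bias (0.063) is under half a standard error. At 30% excluded and c = 0.4 it is about one standard error.

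**The case against.** The primary conclusion rests on the FAS, and no estimate, sample size or decision rule changes. A one-armed attendance criterion follows naturally from testing an add-on, because TAU has no attendance to count. Non-attendance may also be low: participants declare availability for specific weeks before randomisation, the course lasts five days, and FAS entry needs a pre-assessment completed within 14 days before the week. Further detail is left to a statistical analysis plan that is not shown. All of this stands, and it limits the weight of the point. It does not remove it, because the one-sided rule is stated in the article and is not a detail left open.

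Three stronger readings are tempting, and the document does not support them.

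- A reader might infer that the PP analysis is bound to favour TBT-S. Nothing in the document gives an attendance rate or links attendance to prognosis, so the direction is conditional.
- A reader might add contamination of TAU to the same side. If TBT-S works, TAU participants who obtain it elsewhere and stay in the TAU set shrink the contrast, which works against TBT-S. The Discussion also says that no other Norwegian clinic currently offers the adult programme, and access through the trial comes only after the 3-month assessment.
- A reader might conclude that attendance is known only from self-report. The article describes one item but does not say that it is the sole source or that it defines the PP set. Under Interventions it also says that drop-out is tracked systematically, without saying how.

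A fair objection to the remedy is that a complier average causal effect largely rescales the randomised contrast, so it is not an independent robustness check either. That stands. Its merit is that it estimates the effect of attending without discarding randomisation.

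**Conclusion.** The point holds in a limited form. The PP contrast is not protected by randomisation, and its one specific adjustment does not repair this. Under a correlation of 0.3 and 10% to 30% excluded, both assumed, the bias is about 0.05 to 0.12 EDE-Q points towards TBT-S, against the planned 0.44. Over correlations from 0 to 0.4 and up to 30% excluded, it runs from nil to about 0.16, and it reverses if those doing well are the ones who skip days. If the self-report item defines the set, non-return of that form adds a further filter in one arm, whose size cannot be judged from the document. The FAS analysis is untouched, so the consequence is confined to how much reassurance the PP result can give. It should be changed, but it does not threaten the primary result.

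**What to change.** In the statistical analysis plan, which the article says is to be completed before database lock:

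- For the effect of attending, estimate a complier average causal effect on EDE-Q global at 3 months, using the FAS of both arms with allocation as instrument.
- Define receipt as any TBT-S attendance, or as number of days attended. Use the four-day cut-off only as a secondary definition: the estimate is the randomised difference divided by the difference in receipt. If one to three days help as much as four or five, and TAU receives none, the cut-off inflates it by the factor P(any day)/P(four or more days).
- Count any TBT-S that TAU participants obtain before 3 months as receipt.
- Have clinic staff record attendance per day during the week, so that it does not depend on return of the post-assessment form.
- If the PP analysis is kept, label it descriptive.

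The cost is some analysis-plan wording, one further standard analysis and a short daily record at each site. The interval will be wider than for the PP contrast, and the exclusion restriction (allocation acts only through attendance) must be stated; using days attended also assumes a linear effect per day. At submission 31 participants had been randomised, so most attendance can still be recorded prospectively. No sample-size figure changes.
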